### Inclusion/exclusion criteria

In groups 1 and 2, within each cluster, community leaders will be approached to identify literate individuals with specific practices that are recommended by the NIPP approach. These individuals will be invited to become NIPP volunteers. The inclusion criteria for the NIPP volunteers are as follows: willingness to implement the interventions in the circles over a 12-week period, have a healthy child age less than 24 months, and are approved by community leaders. The inclusion criteria for the NIPP female circle participants are as follows: willingness to participate in the group, are planning to stay in the area for 12 weeks, and have a child under the age of 2 (irrespective of nutritional status). The inclusion criteria for the NIPP male circle participants are as follows: willingness to participate, are planning to stay in the area for 12 weeks, and are a spouse, brother, and/or other influential male family members of the female caregiver enrolled in the female circle. There were no specific criteria for the community circle other than being key community leaders. Age is not a direct criterion either for the NIPP volunteers or for the NIPP circle participants though we specifically note that the participant must be a caregiver of a child under the age of 2. In the context of Uganda that caregiver could be a grandmother, adoptive parent, or older sibling, hence, there was no age cut-off. Exclusion criteria for both the NIPP and NIPP+ interventions are as follows: no child under age 2 in the household or not being present in the selected communities during the intervention and data collection periods and/or not willing to participate through the entire 12-week cycle. People can refuse to participate in the interview but continue to participate in the program. There are no specific criteria for default/dropout in the NIPP approach. However, volunteers will visit households where participants have missed 3 consecutive visits to inquire about their participant status. Participants who voluntarily exit the NIPP or NIPP+ program will still be surveyed but may voluntarily decline to participate in the interview at each time point. However, volunteers will visit households where participants have missed a session to inquire about their participant status. If a participant has missed 2 consecutive sessions and cannot be traced or voluntarily exit, they are considered as a defaulter.

### Primary and secondary outcomes

Please see Table 3 for a list of primary and secondary outcomes including the specific measurement and the time point of the measurement. We posit that implementing the NIPP+ approach translates into changes in knowledge and behaviors along with the ability to self-test that result in:
Improved food safety and water quality through the reduction of environmental risk factors as measured by:
Reduced contamination of domestic water within householdsReduced aflatoxin contamination of common staple foodsReduced aflatoxin levels in women and children (blood and urine levels)Improved nutrition and food security through improved household and individual diets and food security as measured by:
Improved dietary diversity in women and childrenImproved household food security

**Table 3 Tab3:** Primary and secondary outcomes

Category	Measure	Time point of measurement	Type of data collection
**Primary outcome measure**			
Nutrition	Women’s dietary diversity Infant and young child dietary diversity	Baseline, endline, 2- and 6-month follow-up, and sustainability	Quantitative
Water quality	*E. coli* (colonies/100 ml) at household and community water source	Baseline, endline, sustainability	Quantitative
	*E. coli* at household and community water		
Food safety	Aflatoxin levels in grain samples Aflatoxin levels (urinary and finger prick)	Endline, sustainability	Quantitative
Food security	Months of adequate household food provisioning, food security access scale	Baseline, endline, and sustainability	Quantitative

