#### COVID-19 reconfiguration

To accommodate safety measures put in place to mitigate the potential spread of COVID-19, both the NIPP and NIPP+ modules were altered to add a session about COVID-19 which included practice on how to properly wear a mask, sensitization about what COVID-19 is, symptoms, and how it is spread between individuals, and additional emphasis on the importance of handwashing with soap or ash to prevent the spread of disease. In addition, each session was amended to begin with a demonstration of proper facemask protocol so that all participants were wearing facemasks correctly for the duration of the program. These additions expanded the standard program design from 12 to 16 weeks.

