### Data collection

Data will be collected on all participants (*n* = 900 in 60 clusters) at the start of the program (baseline), at 4 months after baseline (endline), and at the sustainability measurement (12 months after the end of the intervention) (Fig. 1) by enumerators trained in the proper anthropometric, survey, water collection, and maize collection methods. We will also collect data on a subset of households 2 months and 6 months after the completion of the intervention (“Monitoring Activity” in Fig. 1). We will collect maize samples a few months after endline and a few months after sustainability, which corresponds approximately to September in the intervention year and September in the follow-up year following each year’s harvest. Finally, samples using an in-development smartphone technology for assessing aflatoxin levels in capillary blood will be collected in parallel with the maize aflatoxin data collection (see the “Tools and data collection” section for more detail).

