#### Statistical methods for assessing impact

For the analysis, we will use an intent-to-treat (ITT) approach using the initial randomization of the treatment arms. While we know that there could be some contamination across groups or non-adherence, we will plan for the clusters to be sufficiently far apart that this should limit any bias related to self-selection captured via retention or adherence. Using ITT will allow us to determine the overall impact of having the NIPP vs. NIPP+ vs. control in your community, thus better mimicking real-world program implementation and impact. Each survey question will have the option of “Refused to Answer” or “Don’t Know” and will eventually be transformed into missing variables. Prior to that transformation, we will use the proportion of RA or DK responses to understand the sensitivity of the question itself. We will use the standard rule where if fewer than 5% of your observations are missing, the variable will remain in the analysis. If the 5% or more of observations are missing, we will not use the variable to avoid drawing inaccurate inferences. We will not impute missing data.

For the analysis, we will take advantage of the panel to run mixed effects models, allowing us to determine the role of time-variant and invariant individual household, and community characteristics, as well as measures of exposure and integration on key outcome indicators (Table 1 above). In addition, we will use a difference-in-difference analysis (baseline/endline, baseline/sustainability, endline/sustainability) to triangulate findings. To complement these models, the analysis will also leverage exploratory analysis to identify cross-cutting or underlying correlations using principal component analysis. For all of the analysis, we will control for a host of individual-, household-, and community-level characteristics.

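### If recall exceeds 4 months, the endline value of the primary food-provisioning count includes pre-baseline months, so contrasts that use endline do not compare like with like

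*Protocol article*

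**What the plan says.** The food security row among the primary outcomes in Table 3 reads "Months of adequate household food provisioning, food security access scale", measured at baseline, endline and sustainability. The Data collection section places the two later rounds "at 4 months after baseline (endline), and at the sustainability measurement (12 months after the end of the intervention". The programme was planned for 12 weeks, and the COVID-19 section adds: "These additions expanded the standard program design from 12 to 16 weeks". Endline therefore falls at about the time delivery stops.

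The statistical methods section plans a "difference-in-difference analysis (baseline/endline, baseline/sustainability, endline/sustainability) to triangulate findings" alongside mixed effects models on the panel. No outcome is exempted from any of the three contrasts. The article gives no recall period for the count of months and does not say that the question is shortened at endline. Table 2 bases the sample size on *E. coli* and aflatoxin only.

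**The concern.** A count of months is a property of a window, not of the interview day. When the same count is taken again 4 months later, the two windows overlap unless recall is 4 months or less. The shared months were over before the intervention began, so no arm can change them. The endline score is then partly a second reading of baseline, and the part that can move covers the delivery period rather than the time after it.

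This bears on Aim 3, which is about sustained impact, and on the Introduction's concern that gains present when a project ends may later be lost. The endline/sustainability contrast is where such a loss would be sought. For this outcome it would set a partly pre-intervention window against a fully post-intervention one, so a change in the estimate need not mean a change in the effect.

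**Working it through.** **Inputs.** Baseline-to-endline gap: 4 months (Data collection). Sustainability: 12 months after the intervention ends, so about 4 + 12 = 16 months after baseline. Recall R: not stated, so it is treated as an assumption with a range of 4 to 12 months. The plan has no figure of its own for this outcome to reproduce.

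**Step 1: share of the endline window that predates baseline.** The formula is max(0, R-4)/R.

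| R (months) | Before baseline | After baseline |
|---|---|---|
| 12 | 8/12 = 67% | 4/12 = 33% |
| 9 | 5/9 = 56% | 4/9 = 44% |
| 6 | 2/6 = 33% | 4/6 = 67% |
| 4 or less | 0% | 100% |

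**Step 2: the sustainability window.** At R = 12 it runs from about month 4 to month 16 after baseline. None of it predates baseline, and none predates the end of the intervention. The baseline/sustainability contrast is therefore not diluted.

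**Step 3: size of the baseline/endline attenuation at R = 12.** Suppose the intervention can improve L months of the year. Of these, at least max(0, L-8) and at most min(4, L) fall in the 4 months after baseline. Dividing by L gives the share of the full-year effect that endline can show:

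- L = 12, equal effect in every month: 4/12 = 33%
- L = 10: 20% to 40%
- L = 8: 0% to 50%
- L = 6: 0% to 67%
- L = 4: 0% to 100%

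One third is thus the value under an equal monthly effect, not a ceiling. What is fixed is that only 4 of the 12 months can respond.

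**Step 4: endline/sustainability at R = 12.** Take an equal monthly effect worth 1 month per year, for illustration.

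- Constant effect: endline shows 4/12 = 0.33 and sustainability shows 1.00. The contrast is +0.67 although nothing changed.
- Effect halved after endline: sustainability shows 0.50, which is still above 0.33, so a fading effect looks like growth.
- Break-even: sustainability equals endline when the later monthly effect is one third of the earlier one. Fading of up to two thirds would show no decline.

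**Step 5: matching calendar months.** Months 0 to 4 and months 12 to 16 after baseline are the same four calendar months one year apart. With month-by-month answers, a like-for-like comparison of endline with sustainability is possible.

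**The case against.** The strongest reply is that the premise is not in the article. Recall wording belongs in the questionnaire or the full protocol, and with a recall of 4 months or less there is no overlap. This stands as a limit: the point is conditional and its size depends on R. It does not remove the point, because the article fixes the measure, the 4-month gap and the contrasts, and makes no exception for a longer recall.

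The harm is also narrower than it may look. Pre-baseline months are expected to be balanced by randomisation, so the arm comparison at endline is weakened rather than pushed towards a false effect. The difference-in-difference analysis is there to triangulate, and no passage makes endline the confirmatory time point. All of this stands. It does not rescue the endline/sustainability contrast, whose two windows differ in kind.

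Three stronger readings are tempting, and the documents do not support them.

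- *The endline effect is cut to at most a third.* This needs an equal effect in every month. Food shortage may be seasonal, and Step 3 shows that the share can be higher or lower.
- *Any rise from endline to sustainability is spurious.* Seed and storage would act largely through later harvests, and the plan itself takes maize samples a few months after endline. Some or all of a late gain could be real. The contrast cannot tell the two apart.
- *Endline power collapses.* A reader might borrow the aflatoxin effect size of 0.34 with 17 clusters of 15 and an ICC of 0.05, divide it by 3, and see power fall from 0.84 to 0.16. That effect size belongs to another outcome, and the SD is held fixed. In a change score the shared months cancel. If months were independent and consistently recalled, the SD of change would fall by √3, the effect would be 0.34/√3 = 0.196, and power would be about 0.40. Neither figure is evidence about this outcome.

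**Conclusion.** The concern holds in conditional form. For any recall above 4 months, (R-4)/R of the endline window predates baseline, which is two thirds at R = 12. The baseline/endline contrast for this primary outcome is then generally attenuated, by an amount that depends on which months can improve. The endline/sustainability contrast can show an apparent late gain or hide fading. Under a 12-month recall baseline/sustainability is sound, so the outcome remains usable.

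The conclusion rests on the stated 4-month gap and on the measure being a look-back count. The one-third and +0.67 figures rest further on R = 12 and an equal monthly effect, and are illustrations. The other food security measure in the same table cell, the access scale, is not in question here. The plan should be changed, but the defect does not threaten the trial as a whole.

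**What to change.** State the recall period. If it exceeds 4 months:

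1. Make baseline/sustainability the main contrast for this measure.
2. At endline, compare arms only on the months since baseline, and label the result as a during-programme effect. Those months coincide with delivery, so the result should not be presented as a post-intervention effect.
3. Do not use the full-window count in the baseline/endline or endline/sustainability difference-in-difference.
4. If answers are recorded by month, base any endline/sustainability comparison on the same four calendar months.

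The cost is a line in Table 3 and a line in the analysis text. No new data are needed if months are already recorded one by one; otherwise the question must be asked that way. The downside is a narrower score range at endline.

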**Secondary outcome measures**			
Anthropometry	Child (6–59 months) weight for height *z*-score	Baseline, 2- and 6-month^**.**^ follow-up, endline, sustainability	Quantitative
	Child (6–59 months) weight for age *z*-score		
	Child (6–59 months) height for age *z*-score		
	Child mid-upper arm circumference (MUAC)		
Food security	Purchase and utilization of improved seeds	Baseline, endline, and sustainability	Quantitative
	Purchase and utilization of fertilizer		
	Maize yield		
	Purchase and use of hygrometers, tarps, and hermetic bags	Baseline, endline, and sustainability	Quantitative

The primary outcomes are a change/reduction in specific drivers (risk factors) of malnutrition. Primary outcomes are the outcomes of the greatest interest and are those that are going to be directly affected by the intervention (Vetter and Mascha 2017). Secondary outcomes are those that are affected through the change in primary outcomes. We posit that the identified primary outcomes will reduce malnutrition and improve the nutritional status of infants and young children. Secondary outcomes include child anthropometry (height-for-age, weight-for-age, weight-for-height), water quality (pathogens based on livestock composition along the water chain), and food security and agricultural practices (purchase and utilization of improved seeds, fertilizers, yield, purchase and use of hygrometers and hermetic bags). We do not measure anthropometry as a primary outcome as the goal is to improve (reduce) underlying risk factors. Furthermore, the sample size estimations are based on outcomes that reflect the reduction in risk factors and not reductions in malnutrition.

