**BCC and counseling**		
Fabrication of handwashing facilities	Endline, 2- and 6-month follow-up, sustainability	Quantitative
Fabrication of simple latrines	Endline, 2- and 6-month follow-up, sustainability	Quantitative
Fabrication of fuel-efficient stoves	Endline, 2- and 6-month follow-up, sustainability	Quantitative
Continued use of handwashing facilities	2- and 6-month follow-up and sustainability	Quantitative
Continued use of latrines	2- and 6-month follow-up and sustainability	Quantitative
Continued use of fuel-efficient stoves	2- and 6-month follow-up and sustainability	Quantitative
Infants/young children achieving minimum acceptable diet	Endline, 2- and 6-month follow-up, sustainability	Quantitative
Newborns being exclusively breast fed	Endline, 2- and 6-month follow-up, sustainability	Quantitative
Newborns receiving complementary foods at 6 months	Endline, 2- and 6-month follow-up, sustainability	Quantitative

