#### Anthropometry data collection

Children’s nutritional health status will be measured using standard anthropometric measures: mid-upper arm circumference (MUAC), weight, and height/length and presence of edema. Three measures of each indicator will be taken at the time points specified in Table 2. Female caregivers will also be assessed via anthropometry, specifically weight and MUAC. The enumerator training will be composed of a maximum 2-day training on anthropometry. At the end of the training, enumerators will be tested on the tool and their anthropometry skills. For the latter, we will use the Standardized Monitoring and Assessment of Relief and Transitions (SMART) approach where each enumerator will measure three to five children five times each. Given the importance of collecting accurate anthropometry data, in the field, enumerators will collect three measurements on height and weight for each child.

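### The z-score outcomes start at 6 months of age but children may be enrolled from birth, so the youngest index children have no baseline z-score and join the outcome only at later visits

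*Protocol article*

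**What the plan says.** - **Eligibility** (Inclusion/exclusion criteria): the article notes that "the participant must be a caregiver of a child under the age of 2". The only age-related exclusion is "no child under age 2 in the household". No lower age limit is given.
- **Young infants are in scope**: Table 4, under BCC and counseling, monitors "Newborns being exclusively breast fed".
- **Outcome definition** (Table 3, Secondary outcome measures): the first anthropometry row is "Child (6–59 months) weight for height" z-score. Weight-for-age and height-for-age carry the same 6–59 month band. MUAC, in the same block, carries none. The listed time points are baseline, the 2- and 6-month follow-ups, endline and sustainability.
- **Measurement** (Anthropometry data collection): "Children’s nutritional health status will be measured using standard anthropometric measures", with weight, height or length and MUAC listed, three measurements each, and no age restriction.
- **Analysis** (Statistical methods for assessing impact): besides mixed effects models, "we will use a difference-in-difference analysis (baseline/endline, baseline/sustainability, endline/sustainability) to triangulate findings". The adjusted models control for demographics that include age.

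**The concern.** Table 3 fixes an age band that does not match the children being enrolled. Followed as written, an infant aged 0–5 months at baseline is weighed and measured, but the result is not part of the z-score outcome. The same infant counts once past 6 months. Two things follow for the contrasts that start from baseline:

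- If the analysis uses within-child change, the youngest children drop out of the baseline/endline and baseline/sustainability comparisons, and precision is lost.
- If the analysis compares visit averages, the baseline average covers fewer and older children than the later ones, so a change in who is counted is mixed into the change over time.

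The upper part of the band shows the same poor fit. An index child under 24 months at baseline is under 24 + 16 = 40 months at the last visit, so for index children the band leaves out ages that are enrolled and includes ages that are never reached.

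**Working it through.** **Inputs.** Age at enrolment is 0 to under 24 months (Inclusion/exclusion criteria). The z-score band starts at 6 months (Table 3). Endline is 4 months after baseline and sustainability is 12 months after the intervention ends (Data collection). Taking endline as the end of the intervention, the visits fall at 0, 4, 6, 10 and 16 months from baseline. The sample is 900 children, 300 per arm, 15 per cluster, with an ICC of 0.05 (Sample size calculation and sampling strategy). The article states no age distribution and no share of children under 6 months, so there is no stated figure on this point to reproduce.

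**Share outside the band, uniform ages (assumption).** Share = max(0, 6 − months since baseline) / 24.

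| Visit | Months from baseline | Share under 6 months | Of 900 if all are seen |
|---|---|---|---|
| Baseline | 0 | 6/24 = 25.0% | 225 (75 per arm) |
| Endline | 4 | 2/24 = 8.3% | 75 (25 per arm) |
| 2-month follow-up | 6 | 0 | 0 |
| 6-month follow-up | 10 | 0 | 0 |
| Sustainability | 16 | 0 | 0 |

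The z-score sets would be 675, then 825, then all children, before attrition. The 2- and 6-month visits cover only a subsample of households, so only their zero share matters here.

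**Other assumed age distributions (triangular on 0–24 months).**

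| Shape | Baseline | Endline |
|---|---|---|
| Skewed to older | (6/24)² = 6.3% | (2/24)² = 0.7% |
| Peaked at 12 months | 6²/(24 × 12) = 12.5% | 2²/(24 × 12) = 1.4% |
| Skewed to younger | 1 − (18/24)² = 43.8% | 1 − (22/24)² = 16.0% |

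**Precision if pairs from baseline are dropped.** The variance of an arm mean is proportional to [1 + (m − 1) × ICC] / m per cluster, where m is the number of children contributing. This assumes that the loss is spread evenly over clusters and that the planning ICC of 0.05, set for other outcomes, also applies to change in z-score.

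- Full cluster, m = 15: design effect 1 + 14 × 0.05 = 1.70; 1.70/15 = 0.1133.
- Uniform ages, m = 15 × 0.75 = 11.25: design effect 1 + 10.25 × 0.05 = 1.5125; 1.5125/11.25 = 0.1344. SE ratio √(0.1344/0.1133) = 1.09.
- Skewed to older, m = 15 × 0.9375 = 14.06: 1.653/14.06 = 0.1176. SE ratio 1.02.
- Skewed to younger, m = 15 × 0.5625 = 8.44: 1.372/8.44 = 0.1626. SE ratio 1.20.

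With independent households the uniform case would give 1/√0.75 = 1.155. Clustering makes the loss smaller, because part of the variance lies between clusters and does not depend on m.

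**Endline/sustainability contrast, uniform ages.** m = 15 × 22/24 = 13.75; design effect 1.6375; 1.6375/13.75 = 0.1191; SE ratio √(0.1191/0.1133) = 1.03. This contrast is little affected.

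**The case against.** The case on the other side is substantial, and most of it stands.

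- **Baseline anthropometry is not missing altogether.** A reader might infer that these infants have no baseline anthropometry outcome. MUAC has no age band and the measurement section sets no age limit, so only the baseline z-score, as defined, is absent.
- **A quarter is not a figure from the article.** It follows from uniform ages. Household sampling is purposeful, so uniformity cannot be taken for granted.
- **Bias in the treatment effect is not shown.** Infants pass 6 months on the same calendar in all three arms, so in expectation the shift in who is counted largely cancels in the between-arm contrast. The reservation is that households are selected purposefully after clusters have been assigned, so the share under 6 months could differ by arm. The article does not show that it will.
- **Effects in the youngest children can still be estimated.** A child aged 3 months at baseline is about 7 months at endline and 19 months at sustainability, with z-scores defined at both. A mixed model can use those values without a baseline one, which also reduces the precision loss. Only z-scores before 6 months are lost.
- **Age adjustment is already planned** in the adjusted models.
- **The 5% missing-data rule.** A reader might infer that it would remove the z-scores from the analysis. The article introduces that rule for refused and don't-know survey answers; extending it to children outside an outcome's definition is not supported by the text.
- **The band may have been meant to cover other children in the household**, since Table 3 does not say index child. Even so, enrolled infants under 6 months remain outside it, and the article does not say which children are analysed.

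It might also be said that analysis populations belong in the analysis plan. Here, though, the band is stated in Table 3 and conflicts with stated eligibility, so this is more than an omission.

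**Conclusion.** The mismatch between the enrolment age and the z-score age band is real and should be reconciled. Under uniform ages it removes 25% of index children from the z-score outcome at baseline and 8% at endline, with assumed ranges of about 6–44% and 1–16%, and none afterwards. The cost to the contrasts from baseline is a standard error about 9% larger (about 2–20% over the same range) if incomplete pairs are dropped, and less in a mixed model; otherwise the visits compare different sets of children. These figures rest on assumed ages and on an ICC of 0.05 for change in z-score. Severity is minor to moderate: these are secondary outcomes, the article states that the sample size does not rest on them, and the number of households needed is unaffected.

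**What to change.** In Table 3, define weight-for-height, weight-for-age and height-for-age z-scores for the index child enrolled at baseline, from birth to 59 months, at every visit. Use the WHO standards that the article already applies in cleaning the anthropometry data (Data entry and management), and keep the planned adjustment for age. The 6-month lower limit can be kept for a sensitivity analysis.

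The cost is a wording change: these children are already enrolled, and the measurement section already covers weight and length without an age limit. The downside is that length is noisier in young infants, which the three repeat measurements already planned partly offset.
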